### 2.1. Study Design

The EXEMIG/01 study was a rigorously designed, randomized, controlled, non-blinded interventional trial. This study is non-blinded due to the nature of the intervention, which may introduce performance and assessment bias, particularly with regard to self-reported outcomes. To minimize this risk, standardized procedures, validated questionnaires, and objective measures (e.g., wearable accelerometers) will be used wherever possible.

A total of 200 individuals suffering from episodic high-frequency or chronic MIG (diagnosed following the international criteria outlined in the ICHD Classification 2018 [53]) will be invited to participate voluntarily in this project. Participants will be selected from those attending the Headache Center at Santa Maria della Misericordia Hospital in Perugia, following the usual CUP booking procedures for a neurological consultation. The inclusion criteria were as follows: chronic (≥15 attacks/month, for at least 3 months) or episodic and high frequency (8–14 attacks/month) MIG; age range 18–65 years; PA levels lower than WHO recommendations (engage in 150 to 300 min of weekly moderate-intensity aerobic PA, or 75 to 150 min of vigorous-intensity aerobic activity, or a combination of both that is equivalent [54]); and ability to walk independently. The exclusion criteria were as follows: age younger than 18 years or older than 65 years; clinical evidence of serious cardiovascular, central nervous system, or significant musculoskeletal disease that may limit or contraindicate EXE; and failure to provide written consent for participation in the study.

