All the questionnaires used are presented in the *Measures* section. Participants will complete the questionnaires via a digital form divided into four parts using the Microsoft Forms platform. They will receive a link to voluntarily engage with the forms (the original versions of the project can be accessed at the following links: Part I, https://forms.office.com/e/PW6gAqWVqv (accessed on 3 June 2026); Part II, https://forms.office.com/e/t2hmcpz0Ts (accessed on 3 June 2026); Part III, https://forms.office.com/e/ghJkDLyEEj (accessed on 3 June 2026); and Part IV, https://forms.office.com/e/h6TBgmzM8a (accessed on 3 June 2026). Supervision and assistance from the study team members will be available throughout the process.

(c) Kinesiological assessment of functional capacity, including aerobic capacity, muscular strength, and flexibility, will be performed at the C.U.R.I.A.Mo. Participants will be supervised by kinesiologists specifically trained. Assessment sessions will be preceded by almost one training session to familiarize participants with the machines and the specific protocol of the test. The procedures were reported in the Measures section. Moreover, to objectively evaluate the PA habits, participants will be asked to wear an ActiGraph wGT3X-BT (ActiGraph LLC, Pensacola, FL, USA) for a week.

(d) Comprehensive postural evaluation, categorized into objective, instrumental, functional, and neuromotor examinations.

Initially, a static assessment of overall posture will be performed in an upright position on various planes, observing alignment of the head and neck, symmetry of shoulders and scapulae, spinal alignment and overhang, pelvic position, waist triangles, lower limb alignment, and foot support. The physical examination will be followed by an instrumental evaluation using a plumb line, Bunnel’s scoliometer, measuring tape, goniometer, podoscope, measuring rod, and sit-and-reach test. Barré’s vertical line will be used to determine ascending, descending, mixed, or disharmonious syndrome [57]. The examination will continue in various positions to assess localized or peripheral pain. Functional examinations will evaluate muscle elasticity, mobility, and trophic tone through anterior, lateral flexion, and global extension tests.

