Trophic tones will be assessed with isotonic and isometric evaluations of abdominal muscles, gluteus medius, minimus, maximus, and spinal extensors. Evaluation of spinal curve accentuations, inversions, or extensions, especially dorsal and cervical, will be conducted in the sagittal plane to identify alterations in head posture that may affect MIGs, including specific cervical. The postural examination will conclude with neuromotor tests: Fukuda and Romberg tests (simple, monopodalic, and sensitized) will be used to assess general proprioception and balance [57].

This assessment will be followed by specific tests to evaluate how muscle contracture or weakness, cervical stiffness or instability, and poor posture may influence chronic or episodic MIG, focusing on the neck and cervical-dorsal muscles.

(e) Gnathological assessment will be conducted in accordance with the international diagnostic criteria (DC)/TMD [58]. This involves a thorough medical history of the disorders, followed by an examination of two reference axes. AXIS I focuses on identifying isolated muscle pain, condylar-disk dislocations, arthralgia, or degenerative bone changes within the temporomandibular joints, whereas AXIS II explores the psychological factors that influence the progression of the pathology and chronic pain. Participants will undergo a 4-channel surface electromyography (Teethan) examination [59]. The Baiobit motion sensor will also be used to perform cervical ROM [60,61], balance, and gait tests to identify ascending or descending interference factors in TMD.

After the evaluation, participants will be randomly assigned to two groups: the control group (*n* = 100), comprising people with MIG in standard care; and the intervention group (*n* = 100), comprising people with MIG in standard care plus supervised EXE intervention. Only the second group will attend a supervised, mixed EXE intervention (phase 3).

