#### 2.2.3. Phase 3: EXE Intervention

The EXE program was set to take place at the C.U.R.I.A.Mo. of the Department of Medicine and Surgery at Perugia University. This comprehensive 12-week program will consist of two sessions each week, thoughtfully structured to include mixed activities (aerobic and muscle-strengthening EXEs), and supervised by kinesiologists graduate in Preventive and Adapted Motor Activity Sciences and Techniques (AMPA). Each session will be approximately 60 min in length and will consist of three distinct phases: warm-up, central activity, and cool-down. During the aerobic activities, participants will engage in various EXEs using ergometers, such as treadmills and cycle ergometers, designed to elevate their heart rates to a moderate training intensity, specifically targeting between 40 and 59% of their heart rate reserve. This training section plays an anti-inflammatory role, aiming to enhance cardiovascular fitness, promoting improved endurance, and overall health of the individual. In the muscle-strengthening phase, participants will focus on body-weight EXEs or with small equipment, such as elastic bands and medicine balls, as well as isotonic machines (i.e., lat machine and leg press), targeting, i.e., the neck, shoulders, and upper back. The intensity of these EXEs will be tailored to correspond to 45–50% of the individual’s one-repetition maximum (1RM), ensuring that each participant is trained while maintaining safety and effectiveness.

As participants progress through the program, and if their clinical conditions and abilities allow, there will be a carefully monitored and gradual increase in training intensity of approximately 3–5% every three weeks. The initial sessions were designed to help participants adapt to the EXEs and equipment.

The guidelines provided above serve as a framework that will be adapted to accommodate the specific EXE capacities and needs of each participant, ensuring a tailored and supportive experience for all involved. Adherence to the intervention will be monitored through attendance at supervised sessions and participation in the program. Participants’ adherence to PA recommendations will also be assessed using data from wearable devices. The EXE protocol is standardized to ensure reproducibility across sessions and participants.

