A limitation of this study is its unblinded design, as it is impossible in behavioral intervention research like EXE. Both participants and evaluators knew group assignments, which can introduce bias and potentially overestimate the intervention’s effectiveness. Participants in the intervention group, aware of receiving active treatment and engaging regularly with a kinesiologist, may have developed heightened expectations of improvement, potentially amplifying perceived reductions in pain and quality-of-life gains beyond the actual physiological effects of EXE (enhanced placebo effect). Conversely, control group participants, conscious of not receiving active intervention, may have experienced demoralization, contributing to reduced diary compliance, higher dropout rates, or an overestimation of symptom burden (e.g., demoralization). Furthermore, given the inherently subjective nature of pain assessment, intervention group participants may have been inclined to report more favorable outcomes to justify their investment in the treatment, introducing a degree of social desirability or reporting bias. Finally, the difference between the intervention and control groups likely stems from both the actual impact of exercise and psychological effects due to the lack of blinding, which may result in a larger reported effect size than in blind studies. Moreover, it is crucial to underline that our model will be initially applied to one center (the Headache Center of Perugia). This single-headache center recruitment may limit the study’s generalizability, as participants were drawn from a single clinical site, potentially introducing selection bias. This could affect the external validity of the results, as individuals at one center may not represent the broader migraine population. Future multicenter studies with diverse participants are needed to confirm and extend these findings.

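### The nature of the exercise intervention does not justify unmasked evaluators, so examiner-rated outcomes at 6 and 12 months carry avoidable assessment bias

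*Protocol article*

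**What the plan says.** Section 2.1 gives the blinding status and its reason: "This study is non-blinded due to the nature of the intervention, which may introduce performance and assessment bias". The mitigation offered there is that "standardized procedures, validated questionnaires, and objective measures (e.g., wearable accelerometers) will be used wherever possible".

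The Discussion returns to the point: "A limitation of this study is its unblinded design, as it is impossible in behavioral intervention research like EXE". It then says who is aware of the arm: "Both participants and evaluators knew group assignments, which can introduce bias". The same sentence accepts that the benefit may be overstated as a result. No evaluator is excepted, and neither section distinguishes participants, trainers and assessors.

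On timing, Section 2.2.2 places allocation after the baseline work-up: "After the evaluation, participants will be randomly assigned to two groups". Section 2.2.4 repeats all evaluations at 6 months (T1) and 12 months (T2).

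On location, functional testing and training share a centre. Section 2.2.2(c) says "Kinesiological assessment of functional capacity, including aerobic capacity, muscular strength, and flexibility, will be performed at the C.U.R.I.A.Mo", and Section 2.2.3 says "The EXE program was set to take place at the C.U.R.I.A.Mo". Both tasks are supervised by kinesiologists.

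**The concern.** The stated reason is narrower than the design it is used to support. Supervised exercise cannot be hidden from the person doing it or the person leading it. It can be hidden, at least in part, from someone who sees the participant only for a neck-endurance test or a jaw examination.

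Section 2 names functional capabilities, postural parameters and temporomandibular variables as secondary outcomes, and psychological factors as exploratory. Many of the component measures depend on how firmly the examiner encourages, when a hold is judged to have failed, or how a finding is graded. An examiner who expects exercise to help can shift those readings without intending to. A modest benefit in posture or function could then not be separated from rater expectation, and the trial would have given up a protection it could have had.

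**Working it through.** No figure in the protocol bears on this point, so there is none to reproduce. The check is of the text, followed by an illustration with assumed bias.

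**Step 1: who must know the arm.**
- Participants and the kinesiologists who train them: yes, from the nature of exercise.
- Whoever delivers TPE: yes. The Abstract and Conclusions make TPE part of the intervention, but the article does not say who delivers it.
- Postural examiner, gnathologist, or a kinesiologist who did not train the participant: no reason is given in Section 2.1 or the Discussion.

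The Discussion mentions adapting the exercise programme to postural and gnathological findings. The baseline evaluation can supply those findings, and it precedes randomisation. This need does not require the T1 and T2 examiner to know the arm.

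**Step 2: when the exposure arises.** Baseline ratings are made before allocation and are unaffected, so only T1 and T2 are exposed. The programme lasts 12 weeks. If it starts near baseline (an assumption), training has ended before the 6-month visit, so assessors need not meet participants in the training setting.

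**Step 3: which outcomes are exposed.**

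| Measure | Section | Exposure to the rater |
|---|---|---|
| 6-minute walk, submaximal 1-RM tests | 2.3.4 | Encouragement, end-point call |
| Goniometer range of motion, neck-flexor hold timed by examiner | 2.3.5 | Reading, end-point call |
| Neck-extensor hold to failure or compensation | 2.3.5 | Judgement of failure |
| Manual and visual postural findings | 2.2.2(d) | Clinical judgement |
| DC/TMD examination | 2.2.2(e), 2.3.6 | Clinical judgement |
| Hamilton anxiety scale (called self-administered, but with items completed by the clinician) | 2.3.3 | Interview rating |
| Surface EMG, motion sensor, dynamometer, accelerometer | 2.2.2, 2.3.4, 2.3.6 | Largely instrumented, less exposed |
| Attack counts by diary, most questionnaires | 2.3.1, 2.3.3 | Self-report; assessor masking does not help |

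**Step 4: do the stated safeguards cover the exposed rows?** Questionnaires and accelerometers measure other outcomes. Standardised procedures narrow the room for variation but do not remove expectation in a rater who knows the arm.

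**Step 5: illustration of size.** Inputs: 100 per arm and 30% dropout (Section 2.4, Sample Size), so 100 × (1 − 0.30) = 70 evaluable per arm. The bias b, in SD units, is assumed. With no true effect and a two-sided 5% z-test:

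- SE = √(2/n). For n = 70 it is 0.169; for n = 100 it is 0.141.
- P(reject) = 1 − Φ(1.96 − b/SE) + Φ(−1.96 − b/SE).

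| Assumed bias b (SD) | 70 per arm | 100 per arm |
|---|---|---|
| 0 | 5% | 5% |
| 0.1 | 9% | 11% |
| 0.2 | 22% | 29% |
| 0.3 | 43% | 56% |

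For example, at n = 70 and b = 0.2, b/SE = 1.183 and P = 1 − Φ(0.777) + Φ(−3.143) = 0.219. Section 2.4 also labels d = 0.2 a small effect. It introduces that scale for the exploratory outcomes, so the label applies directly to the clinician-completed scale and not automatically to the secondary outcomes.

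**The case against.** The authors conceal nothing. They disclose the lack of blinding twice, concede assessment bias and accept that the effect may be overestimated. That stands: the defect is the reason given and the missing assessor masking, not a failure to disclose.

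Several functional and temporomandibular measures are instrumented, and Section 2.2.2(c) adds a familiarisation session before testing. That also stands, and it shortens the list of exposed outcomes. The manual, timed and interview-based items remain.

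Full masking may not be workable. Participants may reveal their arm, the person delivering TPE is not identified and could be one of the assessors, and adverse events have to be judged for relatedness to the intervention (Section 2.3.7), which needs the arm. These points limit the fix but do not defeat it. The article gives no staffing numbers, and the Discussion says that the need for specialised personnel already adds complexity.

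Three stronger readings are tempting and are not supported:
- A reader might infer that an unmasked neurologist changes preventive drugs differently by arm. Section 2.2.1 sets the drug plan at enrolment, before randomisation, and no later change is described. The repeat evaluations leave the possibility open, but the documents do not show it.
- A reader might infer that unmasked evaluators are what threatens the primary outcome. Section 2.3.1 takes attack counts from participants' diaries and an online questionnaire. Every mechanism of bias that the Discussion develops is on the participant's side, and masked assessors would not remove it.
- A reader might infer that trainers will retest their own trainees. The shared centre and profession make this possible, but the article does not say who tests whom, and a staffing rota may stand in the full protocol.

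**Conclusion.** The concern holds for examiner-rated secondary and exploratory outcomes at T1 and T2. The article makes a positive choice to leave evaluators aware of allocation, and the reason it gives reaches only participants and staff who deliver exercise or TPE. The resulting bias is avoidable in part, since masking would reduce it but not guarantee its removal.

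Its size is unknown. The 9% to 43% range rests on assumed shifts of 0.1 to 0.3 SD, 70 evaluable per arm and no true effect. It shows how sensitive these outcomes are and is not an estimate for this trial. The primary outcome's main bias, self-report by unblinded participants, is untouched by this point and by its remedy. This is a low-cost improvement to the design, not a flaw that undermines the primary comparison.

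**What to change.** Restate the design in Section 2.1 along these lines: *participants and staff delivering exercise or TPE are unblinded; assessors of examiner-rated outcomes at T1 and T2 are blinded where they do not deliver the intervention.*

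To put this into practice:
- Withhold allocation from the existing postural examiner and gnathologist.
- Have functional tests done by an existing kinesiologist who did not train that participant.
- Have clinician-completed scales rated by someone who does not deliver the intervention.
- State who delivers TPE, so that it is clear which assessors can be masked.
- Ask participants not to reveal their arm, and record every unmasking by outcome and visit.
- Leave adverse-event relatedness and clinical care to unmasked staff.

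In the Discussion, confine the claim that blinding is impossible to participants and intervention staff, and state that the primary outcome remains self-reported and unblinded.

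The cost is a protocol amendment, some scheduling effort and some accidental unmasking, which would be on record. Whether existing staff suffice cannot be confirmed from the article. Where they do not, the outcomes left unmasked should be listed.

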## 5. Conclusions

In the context of MIG, a complex and multifactorial “functional disorder”, a multidimensional approach that extends beyond pharmacological treatment and considers individual lifestyle factors, including EH and metabolic health, may be relevant for clinical management. This study aims to investigate whether an integrated and personalized interdisciplinary approach, characterized by collaboration across various professional disciplines, may contribute to reducing MIG frequency and improving patient-reported outcomes, including quality of life. Within this framework, PA and TPE are the core active components of the intervention; nutritional aspects are included as additional components that act across all groups, potentially modulating metabolic and inflammatory pathways and promoting sustainable lifestyle behaviors. In conclusion, a further strength of the proposed model is the simultaneous assessment of PA behaviors, sedentary time, and EH using both subjective and objective tools. The synergistic interplay among medical treatment, physical education, psychology, and nutrition represents a promising and potentially sustainable framework for the management of chronic MIG, thereby possibly contributing to a broader perspective in the care of this intricate condition.

## Figures and Tables

**Figure 1 nutrients-18-01893-f001:**
[figure not shown]
The EXEMIG01 interdisciplinary model.

**Figure 2 nutrients-18-01893-f002:**
[figure not shown]
Seven day food-headache diary.

**Table 1 nutrients-18-01893-t001:** Multidisciplinary studies.

Authors (Year)	Study Type	Specialists Involved
Golovacheva et al. (2025) [39]	Randomized Controlled Trial (RCT)	Neurologists, CBT specialists, and therapeutic gymnastics specialists.
Sujan et al. (2025) [40]	RCT	Yoga instructors (in addition to standard neurological care).
Tahzeeb et al. (2025) [41]	Cross-sectional Study	Recommends a team including Neurologists and Dentists/Gnathologists for TMD comorbidity.
Hisham et al. (2023) [42]	RCT	Neurologists, researchers, and experts in relaxation training
Helmerson et al. (2021) [43]	Pilot Study	Team for a group-based “migraine school” (like nurses, physiotherapists, psychologists).
Golovacheva et al. (2021) [44]	Case Report	Neurologist, CBT specialist.
De Almeida Tolentino et al. (2021) [45]	RCT	Neurologists, Physiotherapists (including those trained in pain neuroscience education), and researchers
Evans et al. (2020) [46]	RCT	Nutrition scientists, Neurologists, Psychologists, and obesity Specialists
Aguirrezabal et al. (2019) [47]	RCT	Family doctors and neurologists
Cramer et al. (2019) [48]	Prospective Observational Study	Team delivering conventional and complementary medicine (exact composition not specified).
Gaul et al. (2011) [49]	Observational Study	Neurologists, behavioral psychologists, physiotherapists, sports therapists, and specialist headache nurses.
Magnusson et al. (2004) [50]	Comparative Study	Neurologist, psychologist, occupational therapist, and physiotherapist.

**Table 2 nutrients-18-01893-t002:** Nutritional tips for patients with MIG.

Topic and Authors	Practical Recommendations for Patients with MIG
Mediterranean dietary pattern Behrouz V. et al. (2025); Di Lorenzo C. et al. (2023); Arab A. et al. (2023) [20,22,25]	Encourage adherence to a Mediterranean-style dietary pattern rich in vegetables, fruit, legumes, whole grains, nuts, extra-virgin olive oil, and fish; limit ultra-processed foods and excessive saturated fats.
Meal regularity Seng E.K. et al. (2022) [12]	Maintain regular meal timing and avoid prolonged fasting or skipping meals, especially breakfast.
Hydration Ashina M. (2021) [6]	Promote adequate daily hydration and regular fluid intake throughout the day.
Caffeine intake Seng E.K. et al. (2022); Gazerani P. (2020); Nguyen K.V. & Schytz H.W. (2024) [12,34,37]	Moderate and consistent caffeine intake is preferred; excessive consumption or abrupt withdrawal should be avoided. Patients should monitor individual sensitivity.
Alcohol consumption Poboży T. et al. (2025) [26]	Limit alcohol intake, particularly red wine and binge drinking; identify individual trigger patterns.
Ultra-processed foods Cavestro C. et al. (2025); Tu Y.H. et al. (2025) [21,56]	Reduce intake of ultra-processed foods, processed meats, and foods rich in additives when individually associated with attacks.
Trigger foods Poboży T. et al. (2025); Roldán-Ruiz A. et al. (2025); Nguyen K.V. & Schytz H.W. (2024) [26,35,37]	Encourage individualized identification of potential trigger foods using headache and food diaries rather than generalized restrictive diets.
Omega-3-rich foods Di Lorenzo C. et al. (2023); Chen, T.B. et al. (2024) [22,24]	Increase intake of omega-3-rich foods such as fatty fish, walnuts, and seeds.
Weight management Cavestro C. et al. (2025) [21]	Promote healthy body weight through sustainable dietary and physical activity interventions.
Behavioral self-management Demarquay G. et al. (2021); Hisham S. et al. (2023) [9,42]	Integrate dietary education with stress management, relaxation techniques, and therapeutic patient education.

